#### Methods in Analysis to Handle Protocol Nonadherence and Any Statistical Methods to Handle Missing Data

The primary analysis will adhere to the intention-to-treat (ITT) principle with consideration of participants based on their randomized treatment assignment. Protocol nonadherence, such as deviations from the assigned treatment, will be captured and addressed in sensitivity analyses, including per-protocol analyses.

Sensitivity analyses will be conducted to assess the impact of protocol nonadherence on study outcomes. These analyses may include per-protocol analyses, where only participants strictly adhering to the protocol are considered, providing insights into the robustness of the primary ITT analysis.

Multiple imputation methods will be employed to handle missing data. Missing data patterns will be carefully examined, and imputation models will be used to estimate missing values based on observed data, enhancing the completeness of the data set. The missing data mechanism will be assessed to inform the selection of appropriate imputation methods with consideration of mechanisms such as missing completely at random (MCAR), missing at random (MAR), or missing not at random (MNAR).

Imputation models that account for variables associated with missing data, including baseline characteristics, treatment assignment, and relevant covariates, will be developed. The number of imputations will be specified to ensure sufficient imputations to capture uncertainty associated with missing data, commonly using 5 or 10 imputations.

Sensitivity analyses will compare results from the imputed data set with those from observed data to assess the impact of imputation on study outcomes. The methods used to handle missing data will be reported in study publications, transparently communicating any assumptions made during imputation and their potential implications on the study findings.

External validation of imputation models will be considered to enhance the generalizability of imputed data. Collaboration with statistical experts will be sought to ensure the appropriateness and rigor of the chosen methods for handling missing data, with input from experts during the planning phase to adapt methods as needed based on recommendations.

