While the LUCENT protocol presents a comprehensive framework for investigating the outcomes of lung cancer patients in Italy, several limitations should be considered. The study’s reliance on voluntary participation may introduce selection bias, as patients who agree to participate will differ systematically from those who decline. This could impact the generalizability of the findings to the broader population of lung cancer patients. Despite rigorous data collection processes, the accuracy and completeness of the collected data may be subject to human error or inconsistencies across participating centers. The study’s focus on lung cancer patients in Italy may limit the generalizability of the findings to other populations with different health care systems, demographics, or treatment practices. Maintaining high follow-up rates over the study duration may be challenging, particularly if patients experience barriers to participation or drop out due to personal reasons. Lower follow-up rates could introduce bias and affect the validity of longitudinal outcome assessments. The absence of external funding for LUCENT may pose challenges regarding resource allocation, data collection, and study implementation. Limited resources could impact the scale and scope of the study, potentially affecting its ability to achieve comprehensive and robust outcomes. While the protocol emphasizes obtaining informed consent and ethical approval, ethical considerations concerning data privacy, participant confidentiality, and potential risks to participants’ well-being must be monitored and addressed throughout the study. The study’s reliance on specific surgical approaches and centers in Italy may limit the external validity of the findings, particularly in regions with different health care infrastructure or surgical practices. Collaboration with international partners could enhance the study’s external validity.

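### The one missing-data sensitivity analysis that is named cannot test robustness to informative dropout, and the number of imputations is not tied to the amount missing

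*Protocol article*

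**What the plan says.** The section on nonadherence and missing data in the protocol article commits to multiple imputation and makes four statements that matter here.

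- Predictors: "Imputation models that account for variables associated with missing data, including baseline characteristics, treatment assignment, and relevant covariates, will be developed".
- Number of imputations: "The number of imputations will be specified to ensure sufficient imputations to capture uncertainty associated with missing data, commonly using 5 or 10 imputations".
- Mechanism: "The missing data mechanism will be assessed to inform the selection of appropriate imputation methods". All three standard types are then mentioned, from completely random to not at random.
- Robustness: "Sensitivity analyses will compare results from the imputed data set with those from observed data to assess the impact of imputation on study outcomes".

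The section on additional analyses adds a general promise of sensitivity analyses under other assumptions or methods. It is not linked to missing data and names no method for data missing not at random (MNAR). The Discussion acknowledges the threat: "Lower follow-up rates could introduce bias and affect the validity of longitudinal outcome assessments". Both statements of the primary objectives make comparison of individual centres with a national benchmark the main aim. No missing-data rate and no target sample size are given.

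**The concern.** The Discussion names loss to follow-up as a source of bias, but the specific check chosen for missing data is blind to the form of loss that matters most. If sicker patients are the ones who stop answering online questionnaires, imputation under missing at random (MAR) and the observed-data analysis both overstate quality of life, and comparing them would look reassuring.

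Assessing the mechanism does not repair this. Observed data can give evidence against missing completely at random. They cannot separate MAR from MNAR, because the distinction depends on the values that were not seen.

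Two smaller matters sit beside it. The only number of imputations mentioned is a convention unrelated to how much is missing. And the predictor list names treatment but not centre, although centre is the contrast that the primary objective needs.

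**Working it through.** The plan contains no derivation to reproduce. The number of imputations is the only figure in the rule and comes without a calculation. Every missing-data rate, effect size and centre count below is an assumption.

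**1. Imputed versus observed data under informative dropout.** Set-up: outcome y = 0.5x + e, residual SD 1, true mean 0; 3,000 patients; 200 replicates. The log-odds of being missing fall by 0.3 or 0.6 per unit of y, so low scorers drop out more. Imputation uses x and assumes MAR.

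| Missing | Log-odds per unit | Bias, MAR imputation | Bias, observed data | Difference |
|---|---|---|---|---|
| 22% | 0.3 | 0.061 | 0.076 | 0.015 |
| 21% | 0.6 | 0.125 | 0.155 | 0.030 |
| 31% | 0.3 | 0.094 | 0.115 | 0.021 |
| 33% | 0.6 | 0.172 | 0.215 | 0.043 |

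Both estimates are wrong in the same direction. The quantity that the named check examines, the last column, is about a quarter of the bias in the imputed result (for example 0.043/0.172 = 0.25).

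**2. Number of imputations.** With m imputations and fraction of missing information f, the interval width relative to infinitely many imputations is about sqrt(1 + f/m) × t(0.975, df)/1.96, with df approximated by (m − 1)/f².

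- f = 0.5, m = 5: df = 4/0.25 = 16, t = 2.120; sqrt(1.1) × 2.120/1.96 = 1.134.
- f = 0.5, m = 10: df = 9/0.25 = 36, t = 2.028; sqrt(1.05) × 2.028/1.96 = 1.060.
- f = 0.5, m = 50: df = 49/0.25 = 196, t = 1.972; sqrt(1.01) × 1.972/1.96 = 1.011.
- f = 0.2: df = 100 and 225, giving 1.032 (m = 5) and 1.015 (m = 10).
- f = 0.1: df = 400 and 900, giving 1.013 (m = 5) and 1.006 (m = 10).

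Putting (1 + 1/m)f/(1 + f/m) in place of f in the df formula moves the worst case only from 1.134 to 1.152, so the approximation does not drive the result.

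For standard errors reproducible to a 5% coefficient of variation, m = 1 + 0.5 × (f/0.05)² gives 3, 9, 19 and 51 at f = 0.1, 0.2, 0.3 and 0.5. Five or ten is therefore adequate up to roughly f = 0.2 and thin above it. Too few imputations cost precision and reproducibility; they do not cause bias.

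**3. Centre in or out of the imputation model.** Set-up: 30 centres of 100 patients, between-centre SD 0.25 of the residual SD, outcome MAR given one covariate, m = 10, 60 replicates. The measure is the slope of estimated on true centre effects, where 1 means no shrinkage.

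| Missing | Centre omitted | Centre included | Observed data only |
|---|---|---|---|
| 10% | 0.901 | 1.004 | 1.005 |
| 22% | 0.777 | 0.971 | 0.973 |
| 30% | 0.690 | 1.001 | 0.998 |
| 42% | 0.598 | 0.990 | 0.993 |

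If centre is omitted, the shrinkage (1 minus slope: 0.10, 0.22, 0.31, 0.40) roughly equals the missing fraction. If it is included, there is essentially none. The last column also shows that the imputed-versus-observed comparison has a use: it would reveal shrinkage of this kind, although not informative dropout.

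**The case against.** Much can be said for the plan as written. The predictor list is open, so a reader who infers that centre or the outcome is excluded goes further than the text. If completeness differs by centre, centre is itself associated with missingness and falls within the sentence. An outcome being imputed is already in its own model as the dependent variable. The shrinkage in step 3 is therefore conditional on a choice that the article does not make.

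The number of imputations is still to be set so as to be sufficient; 5 or 10 is offered as common practice, not fixed. MNAR is mentioned, and other sensitivity analyses are promised in general terms, so it would be too strong to say that informative dropout will certainly go untested. A full protocol or analysis plan, not shown, would ordinarily carry the detailed imputation model.

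A reader might also infer that quality-of-life values would be imputed after death, because the EQ-5D index is anchored at 0 for death. Nothing in the article says so; the anchor only defines the scale.

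Finally, the article's example of a benchmark is length of stay, and hospital stay is taken from medical records and billing data. Missingness of 20 to 50% is unlikely there.

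All of this stands, and it limits the point. It does not rescue the named check: comparing imputed with observed results is a positive choice, it is the only specific missing-data sensitivity analysis stated, and it cannot do what robustness to dropout requires.

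**Conclusion.** The concern holds in a limited form. The imputed-versus-observed comparison cannot show robustness to informative dropout, and neither assessing the mechanism nor the general promise of further sensitivity analyses supplies a method that can. In the assumed scenarios the check shows a gap of about 0.02 to 0.04 residual SD while the imputed result is off by 0.06 to 0.17. The consequence falls chiefly on quality of life and other follow-up outcomes, not on length of stay.

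The imputation convention is a lesser matter: a 13% or 6% width penalty if half the information is missing, and little at 10 to 20%. Naming centre is a clarification with a large potential effect only where outcome data are appreciably incomplete and centre would otherwise be left out. The document does not support the conclusion that centre differences will shrink under this plan.

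**What to change.** In the missing-data section:

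1. Keep the imputed-versus-observed comparison, described as descriptive. Add a delta-adjusted (tipping-point) MNAR analysis for follow-up outcomes with appreciable missing data, chiefly health-related quality of life. State that the data can inform the imputation predictors but cannot decide between MAR and MNAR.
2. Replace the 5-or-10 convention with a rule: at least as many imputations as the percentage of incomplete cases.
3. Name centre, as a fixed or random effect, among the imputation predictors.

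The cost is a wording change and some computing time. The sensitivity results may be less favourable than those from the present check. Recruitment is planned to the end of 2026 and completion in 2028, so on that timetable the change can be made before the final analysis.

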#### Plans to Give Access to the Full Protocol, Participant-Level Data, and Statistical Code

LUCENT has plans to make the full study protocol publicly accessible, allowing interested parties to review the details of the study. Additionally, the intention is to grant public access to the participant-level data set, promoting transparency and openness in sharing study data. The statistical code used for data analysis will also be made available to the public, allowing researchers and analysts to understand and evaluate the study’s statistical methods.

For dissemination, reputable data-sharing platforms or repositories will be considered to host the protocol, participant-level data set, and statistical code. The study will ensure compliance with ethical standards and legal requirements when granting public access, prioritizing participant confidentiality. Evaluation of embargo periods before public release may allow researchers involved in the study to publish primary findings before more comprehensive access is granted.

Clear documentation outlining the terms and conditions for using the participant-level data set and statistical code will be developed. This includes guidelines to ensure responsible and ethical use of the shared data. To enhance the visibility and accessibility of study-related information, collaboration with reputable data repositories or platforms specializing in hosting and sharing research data will be sought.

Effective communication strategies will be implemented to inform the research community and the public about the availability of the study protocol, participant-level data set, and statistical code. Continuous updates will ensure the most recent protocol version and related materials are accessible to the public. The study aims to foster transparency, collaboration, and reproducibility in research by sharing key study components openly.

### Oversight and Monitoring

The composition of the coordinating center and trial steering committee will be decided. Moreover, the composition of the data monitoring committee, its role, and its reporting structure will be decided.

### AE Reporting and Harm

A systematic approach will be employed to collect AEs, encompassing solicited and spontaneously reported events. A standardized assessment process will be in place to evaluate the severity, causality, and expectedness of each noted AE, with clearly defined criteria for categorizing events as serious AEs.

Reporting mechanisms for solicited and spontaneously reported AEs will be established, and investigators and site personnel will receive training on proper reporting procedures. The study will have a robust system for managing AEs, including immediate actions for severe or unexpected events. It will provide appropriate medical intervention and follow-up for affected participants.

Thorough documentation of each AE will be maintained, including details about onset, duration, resolution, and any actions taken. Data on AEs will be included in study reports and publications. AEs meeting the criteria for reporting to ethics committees and regulatory authorities will be promptly communicated following local regulations and ethical guidelines.

Consideration may be given to establishing a safety monitoring committee to independently review and assess safety-related data and provide recommendations for the trial’s continuation, modification, or termination based on safety considerations.

During the informed consent process, participants will be informed about potential risks and AEs associated with the trial interventions. Regular communication with participants will be maintained to encourage reporting any AEs experienced during the study.

A comprehensive data safety and monitoring plan will be developed, outlining procedures for collecting, assessing, reporting, and managing AEs. The plan will be followed diligently to ensure the highest standards of participant safety.

AE reporting procedures will undergo continuous review, allowing for adaptation based on emerging safety data or changes in the risk-benefit profile of the trial interventions.

### Frequency and Plans for Auditing Trial Conduct

Trial conduct will be audited at planned intervals throughout the study. Procedures for auditing will be detailed to comprehensively examine aspects such as protocol adherence, data integrity, participant safety, and regulatory compliance. The auditing process will be independent of investigators and the sponsor, possibly involving external auditors or separate entities to maintain objectivity.

The scope of audits will cover various aspects, including adherence to the study protocol, informed consent processes, data collection and management procedures, monitoring of AEs, and regulatory compliance. Site selection for audits will be based on risk assessment with consideration of factors like the number of enrolled participants, data quality, and historical site performance, with both random and targeted site selection strategies.

Comprehensive audit reports will be generated, documenting findings, observations, and any identified deviations from the study protocol or regulatory requirements. Recommendations for corrective actions will be included in these reports. In response to audit findings, corrective and preventive measures will be implemented promptly, with collaboration between the study team and auditors to address identified issues.

Audit results, including findings and actions taken, will be communicated to relevant stakeholders to ensure transparency and accountability. The auditing process will be part of the continuous monitoring and improvement framework of the study, informing ongoing quality assurance measures to enhance the overall integrity of the trial. As required, significant audit findings impacting participant safety or data integrity will be reported to regulatory authorities to maintain regulatory compliance.

### Plans for Communicating Important Protocol Amendments to Relevant Parties

A transparent communication strategy will be employed to disseminate information about essential protocol amendments. Significant changes will be notified directly to principal investigators, site personnel, and ethical committees (research ethics committees/institutional review boards). Participants will be informed of modifications that may impact their involvement, emphasizing explicit and understandable communication to maintain trust.

Trial registries will be promptly updated to reflect any protocol changes, ensuring accurate documentation of amendments, including modifications to eligibility criteria, outcomes, and analyses. Journals and publications, if applicable, will be notified of protocol amendments to align with reporting guidelines, and manuscripts will accurately reflect the final protocol.

Regulatory authorities will be informed following local regulations, maintaining timely and compliant reporting for regulatory approval and oversight. Continuous updates will be provided to all relevant parties, ensuring awareness of the study’s evolving nature.

Thorough documentation of protocol amendments and associated communications will be maintained for internal use, audits, and regulatory inspections. A feedback mechanism may allow stakeholders to seek clarification or provide input on protocol changes, fostering open communication and collaboration within the research environment.

### Dissemination Plans

The main results of this clinical study will be published in a peer-reviewed scientific journal.

One of the study chairs will write the final publication based on the final analysis performed by the principal investigators.

Co-authors will be the study’s principal investigators who participate in designing and drawing up the research project. Investigators of foreign centers may be included as authors depending on their contribution to patient assessments and scientific input.

## Discussion

The protocol outlined in LUCENT presents a robust framework for conducting a comprehensive observational study focused on lung cancer patients in Italy. The study’s emphasis on real-world data collection and patient registries provides a valuable opportunity to gather longitudinal data on various aspects of patient care and outcomes, particularly in the context of minimally invasive surgery for lung cancer. One key strength of the protocol is its adherence to the ITT principle, ensuring that participants are analyzed based on their randomized treatment assignment. By incorporating sensitivity analyses to address protocol nonadherence and employing multiple imputation methods for handling missing data, the study demonstrates a commitment to rigor and transparency in data analysis. Furthermore, the protocol’s plan for auditing trial conduct at regular intervals, independent of investigators and sponsors, underscores the importance of maintaining data integrity, participant safety, and regulatory compliance throughout the study. The comprehensive audit reports and corrective actions in response to findings reflect a proactive approach to quality assurance and risk management. The protocol also highlights the importance of transparent communication regarding protocol amendments, ensuring that relevant parties are informed of any significant changes that may impact the study’s conduct or outcomes. By prioritizing clear and explicit communication with participants, ethical committees, and other stakeholders, the study aims to uphold trust and accountability in its research practices. Regarding data sharing and dissemination, the protocol outlines plans to make the full study protocol, participant-level data set, and statistical code publicly accessible. By leveraging reputable data-sharing platforms and repositories, the study aims to promote research transparency, collaboration, and reproducibility while prioritizing participant confidentiality and ethical data use. Overall, the LUCENT protocol demonstrates a comprehensive and meticulous approach to conducting an observational study in lung cancer research. By incorporating robust methods for data analysis, quality assurance measures, and transparent communication strategies, the study sets a strong foundation for generating valuable insights into the outcomes of lung cancer patients undergoing minimally invasive surgery in Italy.

While the LUCENT protocol presents a comprehensive framework for investigating the outcomes of lung cancer patients in Italy, several limitations should be considered. The study’s reliance on voluntary participation may introduce selection bias, as patients who agree to participate will differ systematically from those who decline. This could impact the generalizability of the findings to the broader population of lung cancer patients. Despite rigorous data collection processes, the accuracy and completeness of the collected data may be subject to human error or inconsistencies across participating centers. The study’s focus on lung cancer patients in Italy may limit the generalizability of the findings to other populations with different health care systems, demographics, or treatment practices. Maintaining high follow-up rates over the study duration may be challenging, particularly if patients experience barriers to participation or drop out due to personal reasons. Lower follow-up rates could introduce bias and affect the validity of longitudinal outcome assessments. The absence of external funding for LUCENT may pose challenges regarding resource allocation, data collection, and study implementation. Limited resources could impact the scale and scope of the study, potentially affecting its ability to achieve comprehensive and robust outcomes. While the protocol emphasizes obtaining informed consent and ethical approval, ethical considerations concerning data privacy, participant confidentiality, and potential risks to participants’ well-being must be monitored and addressed throughout the study. The study’s reliance on specific surgical approaches and centers in Italy may limit the external validity of the findings, particularly in regions with different health care infrastructure or surgical practices. Collaboration with international partners could enhance the study’s external validity.

